## Abstract

**Background:**

As disease-modifying therapies (DMTs) for Alzheimer's disease (AD) are becoming a reality, there is an urgent need to select cost-effective tools that can accurately identify patients in the earliest stages of the disease. Subjective Cognitive Decline (SCD) is a condition in which individuals complain of cognitive decline with normal performances on neuropsychological evaluation. Many studies demonstrated a higher prevalence of Alzheimer’s pathology in patients diagnosed with SCD as compared to the general population. Consequently, SCD was suggested as an early symptomatic phase of AD. We will describe the study protocol of a prospective cohort study (PREVIEW) that aim to identify features derived from easily accessible, cost-effective and non-invasive assessment to accurately detect SCD patients who will progress to AD dementia.

**Methods:**

We will include patients who self-referred to our memory clinic and are diagnosed with SCD. Participants will undergo: clinical, neurologic and neuropsychological examination, estimation of cognitive reserve and depression, evaluation of personality traits, *APOE* and *BDNF* genotyping, electroencephalography and event-related potential recording, lumbar puncture for measurement of Aβ_42_, t-tau, and p-tau concentration and Aβ_42_/Aβ_40_ ratio. Recruited patients will have follow-up neuropsychological examinations every two years. Collected data will be used to train a machine learning algorithm to define the risk of being carriers of AD and progress to dementia in patients with SCD.

**Discussion:**

This is the first study to investigate the application of machine learning to predict AD in patients with SCD. Since all the features we will consider can be derived from non-invasive and easily accessible assessments, our expected results may provide evidence for defining cost-effective and globally scalable tools to estimate the risk of AD and address the needs of patients with memory complaints. In the era of DMTs, this will have crucial implications for the early identification of patients suitable for treatment in the initial stages of AD.

**Trial registration number (TRN):**

NCT05569083.

## Background

Research and clinical practice on Alzheimer's disease (AD) are at a turning point. The AD drug development pipeline is leading to new therapies [1], with aducanumab and lecanemab being the first disease-modifying therapies (DMTs) approved for AD [2, 3]. It is widely accepted that DMTs should be administered in the early stages of the disease to halt the pathological process before neurodegeneration begins [4]. Consequently, international research is now focusing on the prodromal and preclinical phases of AD. Subjective cognitive decline (SCD) refers to a self-experienced persistent decline in cognitive capacity compared to the previously normal state. During this decline, individuals exhibit normal age-, sex-, and education-adjusted performance on standardized cognitive tests [5].

SCD has been associated with neuroradiological features suggestive of AD, amyloid deposition [6, 7], and a higher risk of progression to Mild Cognitive Impairment (MCI) or dementia compared to individuals without SCD [8]. Recognizing these associations, the National Institute of Aging-Alzheimer's Association (NIA-AA) has included SCD as the first manifestation of symptomatic AD stages, preceding MCI [9]. Consequently, individuals with SCD may represent a target population for DMT to preserve cognitive function and psychological well-being [10].

However, SCD encompasses a heterogeneous group with various possible trajectories [11] and numerous potential underlying causes, including normal ageing, personality traits, psychiatric, neurological or medical disorders, substance use disorder, and medications [12]. Therefore, it is crucial to identify features and tools that accurately detect prodromal AD among patients with SCD.

In recent years, the Regional Reference Centre for Alzheimer's Disease and Cognitive Disorders of Careggi Hospital in Florence, Italy, has analysed a large dataset of neuropsychological, personality, and lifestyle data collected over approximately 25 years from patients with SCD. This analysis identified demographic [13, 14], cognitive [15, 16], personality [15], and genetic [15] and genetic [13, 17–23] features that increase the risk of progression from SCD to MCI or AD.

This paper describes the protocol of the PREVIEW (PRedicting the EVolution of SubjectIvE Cognitive Decline to Alzheimer's Disease With machine learning) study, which will prospectively investigate baseline predictors and biomarkers of Alzheimer's pathology and progression to MCI and dementia in a large cohort of patients with SCD. In this study, we will integrate our previous findings with data from non-invasive techniques, such as electroencephalography (EEG) and event-related potentials (ERP) recording. These techniques reliably measure neural circuits associated with cognitive processes and may provide sensitive metrics for early diagnosis of cognitive impairment [24]. Additionally, we will employ machine learning approaches, an emerging and promising tool that has demonstrated great potential in diagnosing and classifying neurodegenerative diseases and other medical conditions [25–27].

Specifically, our aims are as follows:i)Integrate a multimodal set of data from SCD patients, including clinical data, neuropsychological assessments, personality traits, cognitive reserve, genetic factors, and features from EEG and ERP recordings.ii)Train and test a machine learning model based on these features to predict biological AD pathology (defined according to CSF biomarkers) and conversion from SCD to MCI and AD dementia through machine learning tools.iii)Define a management protocol for SCD to be applied in memory clinic settings.

The PREVIEW study was registered on ClinicalTrials.gov (registration number: NCT05569083).

## Methods and analysis

### Study design and participants

This is a longitudinal observational cohort study. We will include consecutive patients who self-referred to the Centre for AD and Adult Cognitive Disorders of Careggi Hospital in Florence and are classified as SCD based on SCD-I criteria [5].

We will recruit patients who meet the following criteria:

Iage between 45 and 90 years;IIcomplaining of cognitive decline with a duration of ≥ 6 months;IIIMini Mental State Examination (MMSE) score greater than 24, corrected for age and education;IVnormal functioning on the Activities of Daily Living (ADL) and the Instrumental Activities of Daily Living (IADL) scales [28];Vunsatisfied criteria for MCI [29] and dementia [30];

Exclusion criteria are history of head injury, current neurological and/or systemic disease, symptoms of psychosis, major depression, or substance use disorder (as defined by the Diagnostic and Statistical Manual of Mental Disorders, Fifth Edition [DSM-5] [30]).

The evaluation of exclusion criteria will be conducted through a thorough neurological examination of the patients. The presence of exclusion criteria will be assessed by two independent neurologists. In the event of a disagreement, a third neurologist will be consulted to reach a consensus.

All recruited patients will undergo the following assessments at baseline (T_0_):Icomprehensive evaluation of familial and clinical history;IIextensive neuropsychological assessment, including estimation of premorbid intelligence, evaluation of depression, personality assessment, and assessment of leisure activities;IIIblood collection for measurement of vitamin B12, folic acid, thyroid hormones, as well as *APOE* and *BDNF* genotype analysis;IVEEG and ERP recording.

Patients who provide additional informed consent for lumbar puncture will undergo CSF collection to measure Aβ_42_, Aβ_42_/Aβ_40_ ratio, total tau (t-tau), and phosphorylated tau (p-tau).

Patients will undergo neuropsychological evaluations every two years until progression to AD or other dementias. Based on the results of previous meta-analysis [8], we estimate that a period of six years will be required to reach the desired sample size (see Sect. 2.2). Progression to MCI and AD dementia will be determined based on the criteria established by the NIA-AA [29, 31]. Patients who progress to dementia will be referred to our centre for diagnostic and therapeutic assessments.

A summary of the study design is shown in Fig. 1.

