### Sample size calculation

We estimated the sample size needed for this study using the statistical power of a hypothesis test using the Python module statsmodels [32]. We considered the following parameters:Level of significance (α) = 0.05Statistical power (1-β) = 0.8Effect size (Cohen's d) = 0.6

The required number of patients was 45 per group. Therefore, considering that we aim to compare patients who will show a progression to objective cognitive decline and patients who will not, the total estimated sample size should be 90 individuals.

With an expected conservative drop-out rate of 10%, the number of participants to be included was estimated to be 99 patients.

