### Machine learning classification of patient conditions

Demographic, clinical, cognitive, neurophysiological, and genetic data will be used as candidate input features without any further processing for training a machine learning model. During the training process, a feature selection algorithm will be applied to select the most informative features based on their performance on the validation set.

The machine learning problem will initially be treated as a multi-class classification task. The model will classify patients who are SCD at the time of the measurements into one of the following three classes: stable SCD, progressed to MCI, or progressed to AD dementia. For the subgroup of patients undergoing CSF biomarker analysis, a classification will be performed based on the results of the analysis. Specifically, patients will be classified as carriers or non-carriers of AD pathology, according to the NIA-AA framework [9].

For feature selection, we will test the efficacy of several algorithms including the ANOVA F-test statistic, ReliefF, mutual information, and minimum redundancy maximum relevance (MRMR). The number of retained features for each algorithm will be optimized in the validation loop.

Regarding the classifier models, a set of different machine learning models will be tested, including support vector machine (SVM) with linear, quadratic, cubic, and radial basis function kernels; random forest (RF); gradient boosted trees (xgboost); linear and quadratic discriminant analysis (LDA and QDA); and an artificial neural network (ANN). The hyperparameters of each algorithm will be optimized to determine the model with the best performance in the classification task.

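### The same MCI criteria set entry and the progressed-to-MCI class, with no described use of later visits to check the label, so test-retest variation can create some progressors that baseline scores then predict

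*Protocol article*

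**What the plan says.** All statements come from the protocol article.

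- **Entry** (Study design and participants): inclusion criterion V requires that the MCI criteria of reference 29 are not met.
- **Outcome** (same section): "Progression to MCI and AD dementia will be determined based on the criteria established by the NIA-AA [29, 31". Reference 29 therefore serves both entry and outcome.
- **Visits** (same section): "Patients will undergo neuropsychological evaluations every two years until progression to AD or other dementias". Examinations go on after MCI and end only at dementia. On duration, "we estimate that a period of six years will be required to reach the desired sample size".
- **Model target** (Machine learning classification of patient conditions): three classes, "stable SCD, progressed to MCI, or progressed to AD dementia".
- **Model inputs** (same section): "Demographic, clinical, cognitive, neurophysiological, and genetic data will be used as candidate input features without any further processing".
- **Safeguards**: for eligibility, "The presence of exclusion criteria will be assessed by two independent neurologists", with a third neurologist if they disagree. Nothing comparable is described for the MCI outcome: no confirming visit, no required change from the patient's own baseline, and no class for a patient who meets MCI once and is normal at the next examination.

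**The concern.** A patient who enters just on the normal side of a boundary can fall on the other side two years later with no change in underlying cognition, because any test score varies between occasions. Such patients are not a random sample of the cohort. They are the ones whose baseline scores lay closest to the boundary, and those scores are offered to the model. Part of what the model learns may then be distance to the diagnostic boundary at entry, not early disease.

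Three features of the study make this worth attention.

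- The Discussion names the prognostic value of baseline neuropsychological testing as an open question that the study will help to clarify. That is the association that would be inflated.
- Features are selected on validation performance and are meant to feed a screening and management protocol. Boundary distance could displace EEG/ERP, genetic or personality features, whose own contrasts would be diluted by mislabelled patients.
- The held-out 30% is labelled by the same rule as the training data, so good test-set performance would not expose the problem.

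**Working it through.** **1. The plan's own figure.** Sample size calculation: alpha 0.05, power 0.8, d = 0.6. A two-sided two-sample t-test calculation gives n = 44.59, rounded up to 45, in agreement with "The required number of patients was 45 per group". Then 2 × 45 = 90 and 90 × 1.1 = 99. The figures reproduce.

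**2. Labels arising without any change.** The article gives no score cut-off or reliability, so every input here is an assumption: reliability r of 0.7, 0.8 or 0.9; cut-off c of -1.5, -1.645 or -2.0 SD; one domain, or five domains with true-score correlation 0.4; MCI read as at least one or at least two domains below c; follow-up visits at years 2, 4 and 6; no practice effect or age trend.

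For one domain the single-visit rate has a closed form. With p = Φ(c) and b the probability that two scores correlated r both lie below c, the rate among eligible patients is (p − b)/(1 − p). For c = -1.5 and r = 0.8: (0.0668 − 0.0349)/(1 − 0.0668) = 0.034.

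The other results come from simulation with constant true cognition, 300,000 people per scenario, excluding those who meet the rule at baseline:

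| Rule | r | One visit | At least once in 3 visits | Of 90 | Confirmed at next visit |
|---|---|---|---|---|---|
| 1 domain, c = -1.5 | 0.8 | 3.4% | 7.4% | 6.7 | 2.2% |
| ≥1 of 5, c = -1.5 | 0.7 | 13.7% | 28.1% | 25.3 | 10.3% |
| ≥1 of 5, c = -1.5 | 0.8 | 11.2% | 22.5% | 20.2 | 8.5% |
| ≥2 of 5, c = -1.5 | 0.8 | 3.4% | 7.3% | 6.6 | 2.2% |
| ≥2 of 5, c = -2.0 | 0.9 | 0.7% | 1.6% | 1.5 | 0.5% |

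Over the whole grid, 1.6% to 28.1% meet the rule at least once. About 60% or more of them are normal at the next examination. Requiring confirmation cuts the rate by about 60% to 78%; this column lets a fourth visit confirm the third.

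A second simulation, closer to Table 1 (20 scores in 8 domains, cut-off -1.5 SD, cohort mean 0 to +0.3 SD), gives 9% to 24% if any domain counts, 6% to 16% if two low tests in one domain are needed, and 2% to 6% if only verbal memory counts.

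**3. Do baseline scores predict these labels?** In the first simulation, the lowest or the mean baseline domain score separates the noise progressors from the other stable patients with AUC 0.78 to 0.97; in the second, the lowest baseline domain score does so with AUC 0.84 to 0.93. Nobody has declined in either.

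**4. Effect on other markers.** If a fraction f of 45 progressors carries no marker difference, d becomes 0.6 × (1 − f), and power is approximately Φ(d√(45/2) − 1.96):

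- f = 0.1: d = 0.54, power about 73%
- f = 0.2: d = 0.48, power about 62%
- f = 0.3: d = 0.42, power about 51%

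These are what-if values; f is not known.

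**The case against.** The strongest reply is that the article is condensed and silence is not a rule. A reader might infer that one visit is enough, or that a patient who reverts still counts as progressed. The article says neither. Confirmation and reversion rules may stand in the full protocol or analysis plan, which are not shown. This stands, and the point does not rest on either inference.

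Second, using one set of criteria at entry and at outcome is ordinary in studies of incident MCI and is not an error in itself. The article names a diagnostic framework, not a threshold on test scores, and what reference 29 requires in detail cannot be seen here. This also stands. The rates above belong to an assumed score-based rule, and clinical judgement would lower them by an unknown amount.

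Third, the AUC values come from a setting with no true progression. A reader might take them as the accuracy the model will show, but they say nothing about accuracy in a class that also contains real progressors.

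Fourth, the scope is limited. The CSF-defined classification does not use follow-up test scores, and the Discussion makes it the surrogate target for preliminary analyses. The machine learning section also plans to repeat the procedure on a subset of features. It does not say that the cognitive scores will be left out, so this does not replace the comparison proposed here.

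Fifth, confirmation has its own cost. MCI first seen at year 6 could be confirmed only at year 8, beyond the six-year estimate. Comparing three chances to be labelled with two chances to be confirmed also flatters the confirmed rule. That argues against making confirmation the primary definition, but not against reporting it alongside.

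What survives is the structure: shared criteria at entry and outcome, baseline scores among the inputs, and later visits already planned whose use for the label is not described.

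**Conclusion.** The concern holds as a risk to interpretation of the progressed-to-MCI class and of the baseline cognitive predictors. Under the stated assumptions, between about 2% and 28% of eligible patients with no true change would meet a score-based rule at least once in three visits, roughly 1.5 to 25 of 90. That range is about 18-fold and depends on reliability, cut-off and number of domains, none of which the article gives. It does not support a claim that most MCI progressors would be noise, or any single power figure. The sample-size arithmetic is correct, and the CSF-defined target is outside the problem. The recommendation is an inexpensive improvement, not the correction of a demonstrated error.

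**What to change.** In the section Machine learning classification of patient conditions, add two analyses.

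1. **Confirmed-MCI label.** Count a patient as progressed to MCI only if MCI is found at two consecutive two-yearly examinations, or is followed by dementia. Mark MCI first seen at the last available examination as provisional. Show patients who meet MCI once and are then normal as a separate group, and do not merge them into stable SCD. Report this beside the definition that accepts MCI at any visit.
2. **Models with and without the baseline cognitive scores.** Report the progression models both ways, so that a reader can see how much performance rests on closeness to the diagnostic boundary at entry.

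The cost is one more label derivation and some extra model runs. No visits are added, because patients with MCI are already examined every two years until dementia. The drawback is fewer confirmed progressors at a given date. Confirmation also reduces noise labels without removing them: up to about 10% remained in the least favourable assumed scenario.

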**Fig. 1 Fig1:**
[figure not shown]
Flowchart summarizing the design of the study. Abbreviations: CSF = cerebrospinal fluid; EEG = electroencephalogram; ERP = event-related potentials; AD = Alzheimer’s disease; *BDNF* = brain-derived neurotrophic factor; *APOE* = apolipoprotein

For the purpose of cross-sectional comparison with the SCD group at baseline, two samples consisting of age-matched healthy controls (without cognitive concerns) and MCI patients will undergo EEG and ERP recording.

### Sample size calculation

We estimated the sample size needed for this study using the statistical power of a hypothesis test using the Python module statsmodels [32]. We considered the following parameters:Level of significance (α) = 0.05Statistical power (1-β) = 0.8Effect size (Cohen's d) = 0.6

The required number of patients was 45 per group. Therefore, considering that we aim to compare patients who will show a progression to objective cognitive decline and patients who will not, the total estimated sample size should be 90 individuals.

With an expected conservative drop-out rate of 10%, the number of participants to be included was estimated to be 99 patients.

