The PREVIEW study also has several strengths that deserve emphasis. As mentioned earlier, the use of machine learning is a significant strength and the primary innovative outcome of our project. Another strength is the collection of AD CSF biomarkers, which serves two main purposes: i) given that previous studies have reported an average ten-year period for SCD patients to develop dementia [8, 96], a long follow-up will be necessary to obtain an adequate sample size of patients who progress to AD. By using CSF biomarkers, we can identify patients at a higher risk of AD dementia (according to the ATN system [9]) and classify them as prodromal AD. This classification can be considered as a surrogate target for preliminary cross-sectional analyses; ii) as mentioned earlier, SCD can also be the first clinical manifestation of medical conditions other than AD. CSF biomarkers will enable us to differentiate SCD with Alzheimer's pathology from SCD due to other causes. It should be noted that our study includes patients who self-refer to our memory clinic, as recommended by previous studies, to reduce sample heterogeneity and increase the chances of identifying subjects with preclinical AD compared to community-based studies [116]. Finally, we would like to emphasize that all the features considered as potential predictors will be derived from non-invasive, relatively inexpensive, and easily accessible techniques.

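### The 80% power rests on a near-equal split of progressors and non-progressors, which a consecutive cohort does not secure and no stated progression proportion supports

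*Protocol article*

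**What the plan says.** The Sample size calculation section reports that the number was obtained "using the statistical power of a hypothesis test using the Python module statsmodels", with α = 0.05, power 0.8 and Cohen's d = 0.6. The result is "The required number of patients was 45 per group". The groups are then defined by outcome: "we aim to compare patients who will show a progression to objective cognitive decline and patients who will not". From this the section concludes that "the total estimated sample size should be 90 individuals", and adds: "With an expected conservative drop-out rate of 10%, the number of participants to be included was estimated to be 99 patients".

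Study design and participants describes how patients enter: "We will include consecutive patients who self-referred to the Centre for AD and Adult Cognitive Disorders of Careggi Hospital". There is no sampling by outcome and no target number of progressors. Follow-up is every two years and ends only at dementia. On timing, citing a meta-analysis, the section says "we estimate that a period of six years will be required to reach the desired sample size".

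The Discussion cites the same meta-analysis, with another source, for the statement that "previous studies have reported an average ten-year period for SCD patients to develop dementia". It adds that a long follow-up will be needed to collect enough patients who progress to AD. No section gives an expected proportion of progressors.

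**The concern.** Doubling a per-group number gives the total only when the investigator fixes the group sizes. Here nature fixes them. Of 90 completers, the progressor group is 90 times the progression proportion, and the remainder did not progress. The step from 45 to 90 therefore contains an unstated assumption of about 50% progression.

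If fewer progress, the smaller group governs precision and the stated power is not met. This calculation is the only justification the article gives for the cohort size. The number of progressors also limits the machine-learning work, which divides them further into MCI and AD dementia and holds out 30% of the data for testing. As an illustration only, 22 progressors (about 25% of 90) would put about 0.3 × 22 = 6.6, or 7, in the test set across two classes.

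**Working it through.** **Inputs.** From Sample size calculation: α = 0.05, power 0.80, d = 0.6, 90 completers. Sidedness is not stated. The progression proportion is not stated either, so it is an assumption here and is shown as a range.

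**Reproducing the plan's figure.** A two-sample t-test with equal groups, two-sided, needs 44.59 per group, so 45. Power at 45 versus 45 is 0.804. A one-sided test needs 35.04, so 36, which does not match. The plan's figure is therefore correct for a two-sided test with a 1:1 split.

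**Drop-out.** 90 × 1.10 = 99, whereas 90 / 0.90 = 100. The difference is one patient and does not matter here.

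**Unequal groups.** With n1 progressors and n2 = 90 − n1 non-progressors, the non-centrality is λ = d × √(n1·n2/90) on 88 degrees of freedom. Power is the probability that the non-central t exceeds the two-sided 5% critical value of 1.987 in absolute size. The detectable d at 80% power is 2.833 / √(n1·n2/90), where 2.833 is the λ that gives 80% power. For 45 versus 45 this is 2.833 / 4.743 = 0.60.

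| Progressors / others | Share progressing | √(n1·n2/90) | λ at d = 0.6 | Power | Detectable d |
|---|---|---|---|---|---|
| 45 / 45 | 50% | 4.743 | 2.846 | 0.804 | 0.60 |
| 41 / 49 | 46% | 4.725 | 2.835 | 0.801 | 0.60 |
| 36 / 54 | 40% | 4.648 | 2.789 | 0.788 | 0.61 |
| 35 / 55 | 39% | 4.625 | 2.775 | 0.784 | 0.61 |
| 27 / 63 | 30% | 4.347 | 2.608 | 0.732 | 0.65 |
| 22 / 68 | about 25% | 4.077 | 2.446 | 0.677 | 0.69 |
| 18 / 72 | 20% | 3.795 | 2.277 | 0.615 | 0.75 |

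At 40 versus 50 power is 0.799, so 41 progressors is the smallest number that keeps 80%. Power is flat near 1:1: the loss is under 2 percentage points from the 80% target down to 35 progressors and becomes material below that.

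**The case against.** Three points on the other side carry weight.

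First, a reader might infer that 80% power needs half of the cohort to progress. It does not. As the table shows, 46% is enough, and 39% still gives about 78%.

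Second, a reader might set the Discussion's ten-year average against the six-year horizon and conclude that the article itself points to far fewer than 45 progressors, so that the study lacks its stated power. The documents do not support this. The ten years refers to dementia, whereas the sized comparison counts any progression to objective decline, including MCI, which comes earlier. Suppose ten years is read as an exponential time to dementia. Dementia alone would then reach 1 − 0.5^0.6 = 34% by six years if ten years is the median (31 versus 59, power 0.763), or 1 − e^(−0.6) = 45% if it is the mean (41 versus 49, power 0.801), before any MCI is added. This does not rescue the plan either, because it assumes that every patient eventually develops dementia. The Background describes SCD as heterogeneous, with causes that include normal ageing, and the ten years may describe converters only. The text settles the proportion in neither direction.

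Third, the six years is tied to a meta-analysis not available here, follow-up is open-ended so progressors can keep accruing, and CSF status is offered as a surrogate target for preliminary analyses. A fuller protocol might also hold the missing proportion. These points soften the criticism of the timeline. They do not justify the printed calculation, which presents 90 as following directly from 45 per group.

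**Conclusion.** The concern holds in conditional form. The figure of 45 per group is right for equal groups, but the 90/99 total and the 80% power rest on a near-equal split that the design does not secure and no stated proportion supports. The stated power holds if about 46% or more of 90 completers progress to MCI or dementia. If the share is 40% the loss is trivial. At 20% to 30%, power is 0.615 to 0.732 and the detectable effect is 0.75 to 0.65 instead of 0.6.

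These figures assume a two-sided t-test, d = 0.6 and exactly 90 completers, with the progression share as an outside assumption. They do not show that the study will be under-powered or that progressors will fall well below 45. They show that the claim of 80% power is unsupported as written.

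**What to change.** In Sample size calculation, state the expected proportion progressing to MCI or dementia by six years, with its source. The cited meta-analysis, or the centre's own SCD data of approximately 25 years described in the Background, are natural candidates. Recompute power for that unequal split, and replace the single 80% figure with power or detectable d over a plausible range, as in the table above. State that the test is two-sided.

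In Study design and participants, say what the desired sample size means (patients enrolled, or progressors observed). Explain how six years fits the Discussion's remark on long follow-up, making clear that the remark concerns progression to AD dementia only, whereas the sized endpoint includes MCI.

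The cost is one rewritten paragraph and one clarifying sentence. No extra enrolment is required; the downside is that the stated power may become less favourable. If the sponsor prefers to keep 80% power at d = 0.6, the completers needed are 93, 106, 119 and 139 at 40%, 30%, 25% and 20% progression. Dividing by 0.9 gives 104, 118, 133 and 155 enrolled. That choice is the sponsor's.

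### Minor arithmetic slip: 99 enrolled with 10% drop-out leave an expected 89.1, not the required 90; dividing by 0.9 gives 100

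*Protocol article*

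**What the plan says.** All the figures stand in the protocol article under Sample size calculation. The inputs are a significance level of 0.05, power of 0.8 and a Cohen's d of 0.6, with the calculation done "using the statistical power of a hypothesis test using the Python module statsmodels". The result is given as "The required number of patients was 45 per group". The two groups are patients who progress to objective cognitive decline and patients who do not, so "the total estimated sample size should be 90 individuals". The section then applies the allowance for drop-out: "With an expected conservative drop-out rate of 10%, the number of participants to be included was estimated to be 99 patients".

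The formula for the drop-out allowance is not printed. No other section of the article gives a different enrolment target.

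**The concern.** The article prints three linked figures: the number required at analysis (90), the expected loss (10%) and the number to be included (99). They do not agree. Drop-out acts on the patients who enter the study, so the enrolment target has to be large enough that 90% of it is at least 90. Taking 10% of the smaller, final number and adding it back always falls a little short.

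What is at stake is limited. The printed target sits marginally below the plan's own criterion of 45 per group and 80% power. Because the article states all three numbers, this is a wrong figure and not a detail that a condensed article may leave to a fuller document.

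**Working it through.** **Inputs, all from Sample size calculation:** d = 0.6, α = 0.05, power = 0.80, 45 per group, 90 in total, drop-out 10%, 99 to be included.

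**Assumptions needed to reproduce the figures:** the article does not state whether the test is one- or two-sided, or which statsmodels routine was used. A two-sided, two-sample t-test with equal groups is assumed because it returns the stated 45; a one-sided test would need about 35 per group.

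**Step 1: reproduce 45 and 90.** The statsmodels two-sample t-test solver returns 44.586 per group. Rounded up, this is 45, and 2 × 45 = 90. Both match the article.

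**Step 2: reproduce 99.**
- Adding 10% to the requirement: 90 × 1.10 = 99. This matches exactly.
- Dividing by the retained share: 90 / (1 − 0.10) = 100. This does not match.

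**Step 3: apply the stated drop-out to each target.**
- 99 × 0.9 = 89.1, which is 0.9 below 90.
- 100 × 0.9 = 90, as required.

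**Step 4: see whether rounding rescues 99.** The unrounded total requirement is 2 × 44.586 = 89.17, and 89.17 / 0.9 = 99.08, which still rounds up to 100. A normal approximation gives 44 per group, 88 in total, and 88 / 0.9 = 97.8, rounded up to 98, so 99 would then be enough. But the article states 45 and 90, so the normal approximation is not its calculation.

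**Step 5: effect on power** (two-sided t-test, d = 0.6, α = 0.05):

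| Evaluable patients | Power |
|---|---|
| 45 + 45 = 90 | 0.804 |
| 44 + 45 = 89 | 0.799 |

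The difference is 0.8037 − 0.7992 = 0.0045, about 0.5 percentage points.

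**The case against.** The strongest reply is that the slip has no practical consequence, and most of that stands. The article gives power to one decimal, and 0.799 rounds to 0.8. Before rounding, the gap is 89.17 − 89.1 = 0.07 of a patient. The figure of 99 is described as an estimate for a cohort of consecutive self-referred patients, and nothing in the article says that recruitment stops there, so one patient more or less is within ordinary variation. None of this makes 99 the right result of the stated inputs, but it does fix the weight of the point as minor.

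Two stronger readings are tempting, and the article does not support either as part of this point.

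- **That attrition will be much heavier than 10%, so the shortfall is really large.** A reader might infer this from the evaluations every two years and the six-year horizon in Study design and participants. The article contains no attrition data, so any other annual rate would be an outside assumption. It also does not say that the 10% is cumulative over six years; the six years are given as the time needed to reach the desired sample size. Heavier loss would challenge the 10% input and not the inflation step, and a target of 100 would not cure it. The period that the 10% covers is detail that a condensed article may leave out, and whether it deserves to be called conservative cannot be judged from the text either way.
- **That enrolling 100 restores 80% power.** The groups are defined by outcome and are not allocated. With 100 enrolled and 10% lost, 90 patients are expected, but not 45 in each group. For illustration, with 90 analysed and assumed progression shares of 10% to 40%, power would be about 0.39 to 0.79. That is a separate matter and much larger than the one-patient slip.

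**Conclusion.** The figure of 99 is wrong on the plan's own inputs. With 90 required and 10% expected to drop out, the number to be included is 100. The printed target leaves an expected 89.1 patients, in practice one short, and lowers power from 0.804 to 0.799.

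The conclusion about 99 against 100 rests only on the printed 90 and 10%, with drop-out read in the usual way as a share of those enrolled. That the allowance was added to 90 is inferred from the exact match with 90 × 1.10, since the formula is not shown. The power figures rest further on a two-sided t-test and on the plan's equal split.

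This is a minor arithmetic correction. It would not change any decision about the study, and it is not evidence that the study is underpowered.

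**What to change.** In Sample size calculation, do one of the following:

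- restate the number to be included as 100, showing 90 / (1 − 0.10) = 100; or
- keep 99 and state that about 89 evaluable patients are expected, with power of about 0.799 at 44 against 45 under the equal-split assumption.

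In either case, do not present the corrected number as guaranteeing 45 progressors and 45 non-progressors. The first option costs one number in the text and one more patient in a consecutive clinic series; the second costs one sentence.
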